## Abstract

**Background:**

Diabetic retinopathy (DR) is the leading cause of blindness in type 1 Diabetes Mellitus (DM) patients, as a consequence of impaired blood flow in the retina. Optical coherence tomography angiography (OCTA) is a newly developed, non-invasive, retinal imaging technique that permits adequate delineation of the perifoveal vascular network. It allows the detection of paramacular areas of capillary non perfusion and/or enlargement of the foveal avascular zone (FAZ), representing an excellent tool for assessment of DR. The relationship of these microvascular changes with systemic factors such as metabolic control or duration of the disease still needs to be elucidated.

**Methods:**

Prospective, consecutive, large-scale OCTA study. A complete ocular examination including a comprehensive series of OCTA images of different scan sizes captured with 2 OCT devices (Cirrus HD-OCT, Carl Zeiss Meditec, Dublin, CA, USA, and Triton Deep Range Imaging OCT, Topcon Corp, Topcon, Japan) will be obtained as part of the yearly routine follow up visits in type 1 DM patients seen in the Diabetes Unit of the Endocrinology department which give written informed consent to participate in the project. The aim of this study is to investigate the relationship between OCTA-derived parameters and systemic factors, as metabolic control (Hb1Ac, lipid profile, cholesterol, etc), and other relevant clinical factors as demographics or duration of the disease.

**Discussion:**

This study is directed to investigate the relationship between the status of the perifoveal vascular network and systemic markers of the disease, and in particular to study whether these changes reflect those occurring elsewhere in the body affected by diabetic microvascular disease, as the kidneys or the brain. If these relationships were demonstrated, early detection of these microvascular changes by OCTA could lead to modifications in the pharmacological management of type 1 diabetic patients, as a way to reduce the risk of future complications in both the eye and other organs.

**Trial registration:**

ClinicalTrials.gov, trial number NCT03422965.

## Background

Diabetic retinopathy (DR) is the most important cause of blindness in type 1 DM patients [1, 2]. It has been postulated that selective loss of pericytes and thickening of the basement membrane in retinal capillaries occur as a result of exposure to elevated blood glucose over an extended period of time, damaging the retinal vessels and affecting the retinal blood flow in a time-dependant manner [3]. To evaluate the vascular flow in the retina of diabetic patients, fluorescein angiography (FA) requires an intravenous injection and has been relegated by the advent of non-invasive retinal imaging techniques [4–10] Optical coherence tomography (OCT) is a light-based technique that provides pseudo-histologic images of the retinal structure, which has become the main diagnostic tool in the management of retinal diseases [11]. Unfortunately, the information given by conventional OCT images is merely structural, and no information about blood flow or perfused areas can be obtained, being difficult to detect early changes in the retinal vascular network of diabetic patients.

Recently, a novel OCT-based technique called OCT angiography (OCTA) has been developed [12]. This OCTA technique is based in a newly developed software that employs an image processing algorithm, which analyses the decorrelation of the signal received by the OCT in a specific geographic location at two different timepoints. Similar to Doppler ultrasonography, the detection of two consecutive signals in a retinal vessel allows the detection of blood flow, and permits a two-dimensional reconstruction of the retinal vascular network. The main advantage of this technique is that it does not need the use of an intravenous dye, and therefore can be performed in a day-by-day basis in all patients. In the field of diabetic retinopathy, OCTA represents an interesting opportunity to evaluate the status of the perifoveal vascular network at different times of the disease, to identify early changes such as capillary dilation, enlargement of foveal avascular zone (FAZ), paramacular areas of capillary nonperfusion and presence of microaneurisms in a non-invasive way [13–18].

These preclinical alterations could be correlated with systemic factors such as time of diabetes evolution and metabolic control, and may also reflect those occurring elsewhere in the body affected by diabetic microvascular disease. Early detection of these changes could lead to modifications in the pharmacological management of patients to avoid microvascular complications in both retinal level and in other organs, such as the renal glomerulus.

The aim of this ongoing study is to evaluate the role of OCTA as a non-invasive screening tool for detecting early changes in the perifoveal vascular network in a large series of type 1 DM patients. The objectives of this project are to study the characteristics of the perifoveal capillary network using OCTA in patients with type 1 DM and controls, patients with type 1 DM with and without diabetic retinopathy, and patients with type 1 DM at different times of disease progression. Moreover, it is also directed to evaluate associations between the characteristics of the perifoveal capillary network with demographic factors, metabolic control and other risk factors in type 1 DM patients.

## Methods

### Study design

Cross sectional, exploratory study in a cohort of type I DM patients seen in the Endocrinology service in a 36-month period from May 2017, with prospective collection of OCTA images and relevant clinical data. This study is registered in the Clinical Trials website (ClinicalTrials.gov, trial number NCT03422965). The Standard Protocol Items Recommendations for Interventional Trials (SPIRIT) 2013 checklist was addressed in the present paper (Additional file 1).

### Ethics

This study was approved by the Institutional Review Board of Hospital Clinic of Barcelona (study protocol version 0.2, 23/11/2016). Written informed consent will be obtained for all participants.

### Study population

Type I Diabetes Mellitus patients undergoing yearly follow up visits as per routine clinical care at the Diabetes Unit of the Endocrinology service of our center will be asked to participate in the study (Fig. 1).

**Fig. 1 Fig1:**
[figure not shown]
Patient flow diagram. Type 1DM patients seen in the Endocrinology service for their yearly revision will be invited to participate in the study (Researchers 6, 7 and 8). Those willing to participate will give informed consent and will be referred to the Ophthalmology service for a complete eye examination (Researcher 5) which include capture of a comprehensive battery of OCT and OCTA image datasets (Researcher 9). These images will be evaluated (Principal investigator and researchers 1–4) and processed with commercial and research softwares (Researcher 10) to obtain objective measurements of OCTA derived parameters (i.e. vessel density, etc.) which will be correlated to systemic markers (i.e. glycated haemoglobin, etc.)

### Sample size

Given that no normative databases are available for vessel density in normal eyes the project was designed in an exploratory basis. In our hospital, an estimate number of 2000 type I DM patients are seen in a yearly basis, which will be offered to enter the study voluntarily. All patients willing to participate during the study period will be included. We anticipate an estimated opt-out rate of 50%, with a final estimated sample size of 1000 patients.

### Inclusion and exclusion criteria

Patients with concomitant ocular pathology other than diabetic retinopathy detected in the ocular examination (uveitis, glaucoma, etc.) will be excluded from the analysis. Patients with inability to perform retinal images and ocular examinations (OCT, OCTA, fundus retinographies, biometry, etc.) or give written informed consent will not be included in the study.

### Study groups

Type I DM patients with and without existing diabetic retinopathy (DR) will be included in the study. Both groups will be classified by duration of diabetic disease (defined as date of type I DM diagnosis), in 3 main groups: A. ≤5 years from diagnosis, B. > 5 - < 15 years from diagnosis, and C. ≥15 years from diagnosis. Subgroup analysis will include also treatment type, glycemic control (glycaemia and HbA1c), body mass index, lipid profile and kidney function tests. A cohort of 100 normal eyes (controls) from a pool of healthy volunteers with clear media and without retinal disease will undergo retinal imaging with OCTA for comparison with type 1 DM cases images.

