### Interventions

#### Systemic data

Systemic status of the diabetic disease will be evaluated in routine clinical care examinations in the Diabetes Unit of the Endocrinology service, and clinical data collected will include: Demographics, date of diagnosis, duration of disease, treatment type, glycaemia, HbA1c levels, concomitant pathology (hypertension, etc.), body mass index, lipid profile (total cholesterol, triglycerides, HDL-cholesterol, LDL-cholesterol) and kidney function tests (urinary albumin excretion, estimated filtration glomerular rate).

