### Statistical methods

Descriptive and frequency statistics will be used to assess qualitative variables. Normality of quantitative variables (i.e. pixel area) will be examined using histograms and the Kolmogorov-Smirnov test protected by the Bonferroni correction. To assess differences in quantitative measurements between study groups, parametric and non-parametric tests will be performed as appropriate, respectively. Correlation between clinical data and OCTA derived measurements will be analyzed using a multivariate regression model to assess the effects of clinical characteristics on these values. Visual acuity measured in Snellen notation was converted to logMAR (logarithm of the minimum angle of resolution) equivalents for the purposes of statistical analysis. VA values recorded as counting fingers (CF), hand movements (HM), and perception of light (PL) were converted to 2.1, 2.4, and 2.7 LogMAR, respectively. A *p* value of less than 0.05 will be considered statistically significant. All statistical analysis will be performed using IBM SPSS Statistics software version 21.0 (IBM Corp., Armonk, NY, USA).

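### Two of the four main comparisons test diabetes duration only as three classes, although date of diagnosis and duration are collected; continuous duration should be the main duration analysis

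*Protocol article*

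**What the plan says.** The Study groups section of the protocol article divides type 1 diabetes patients by DR status and then by duration: "Both groups will be classified by duration of diabetic disease (defined as date of type I DM diagnosis), in 3 main groups". The classes are "A. ≤5 years from diagnosis, B. > 5 - < 15 years from diagnosis, and C. ≥15 years from diagnosis".

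Main outcome measures lists four comparisons for vessel density, total avascular area and the foveal avascular zone. The last two compare duration timeframes, first in eyes without DR and then in eyes with DR.

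Statistical methods gives the test for such comparisons: "To assess differences in quantitative measurements between study groups, parametric and non-parametric tests will be performed as appropriate". The same section plans a second analysis: "Correlation between clinical data and OCTA derived measurements will be analyzed using a multivariate regression model to assess the effects of clinical characteristics". It does not say whether duration enters that model, or in what form.

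Systemic data shows what is recorded: "Demographics, date of diagnosis, duration of disease, treatment type, glycaemia, HbA1c levels".

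The Sample size section calls the project exploratory and reaches 1000 patients from clinic volume and an expected opt-out. It gives no effect size, standard deviation or power target.

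**The concern.** The relation between the retinal vessels and duration of disease is one of the questions the study exists to answer. The Abstract calls it unresolved and names duration in the aim, and the Background lists time of disease progression among the objectives. Yet the comparisons named as main replace a measured quantity with three labels.

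Three things are lost.

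- **Power.** If the outcome changes steadily with duration, variation in duration within a class no longer counts towards the test.
- **Shape.** Three class means cannot separate a steady decline from an early drop with a plateau, or from a late acceleration.
- **Long durations.** Every patient at 15 years or more shares one class, so 15 and 40 years count as the same exposure and any trend beyond 15 years cannot be seen.

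**Working it through.** **The plan's own figure.** 2000 × (1 − 0.50) = 1000 patients. This reproduces. It is a feasibility figure, and there is no power calculation to check.

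**Inputs.** From the protocol: cut points of 5 and 15 years, and significance at 0.05 (taken as two-sided). Assumed, because the protocol gives no figure: the distribution of duration, a linear relation, 600 patients without DR, one value per patient, and the correlation ρ between duration and the outcome.

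**Step 1: information kept by the classes.** For duration uniform on 0 to U years, the share kept is the between-class variance divided by the total variance, U²/12.

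For U = 40:
- class weights: 5/40 = 0.125, 10/40 = 0.25, 25/40 = 0.625
- class means: 2.5, 10 and 27.5; overall mean 20
- between-class variance: 0.125 × 17.5² + 0.25 × 10² + 0.625 × 7.5² = 38.28 + 25.00 + 35.16 = 98.44
- total variance: 1600/12 = 133.33
- share kept: 98.44/133.33 = 0.738

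| Assumed range | Between-class | Total | Share kept |
|---|---|---|---|
| 0-30 years | 62.5 | 75.0 | 0.833 |
| 0-40 years | 98.4 | 133.3 | 0.738 |
| 0-50 years | 135.0 | 208.3 | 0.648 |

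**Step 2: where the loss arises.** For U = 40 the within-class variance is 133.33 − 98.44 = 34.90 (from unrounded values). The top class contributes 0.625 × 25²/12 = 32.55, or 93% of it. The corresponding figures are 75% for 0-30 years and 97% for 0-50 years. Most of what is discarded therefore lies in the open class from 15 years upwards.

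**Step 3: power.** The continuous test has 1 degree of freedom and noncentrality λ = nρ²/(1 − ρ²). The three-class test has 2 degrees of freedom, with ρ² replaced by kρ², where k is the share kept. Power is the upper tail of the noncentral F distribution beyond its 5% critical value.

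For n = 600, ρ = 0.12 and k = 0.74:
- continuous: λ = 600 × 0.0144/0.9856 = 8.77, power 84%
- classes: λ = 600 × 0.010656/0.989344 = 6.46, power 62%

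| ρ | Continuous | Three classes (k = 0.74) | Loss (points) |
|---|---|---|---|
| 0.12 | 84% | 62% | 22 |
| 0.15 | 96% | 82% | 14 |
| 0.20 | 99.9% | 97.6% | 2 |
| 0.25 | 100% | 99.9% | about 0 |

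**Step 4: other distributions.** Fix the effect so that continuous duration has about 80% power. The three-class test then has about 62% (uniform 0-30 years), 57% (uniform 0-40), 49% (exponential, mean 15 years; 62% of variance kept) or 42% (gamma, mean 20 and SD 11 years; 51% kept). Results are nearly the same for 200, 500 and 1000 patients.

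**Step 5: the DR class with at most 5 years' duration.** Its size is 1000 × (share of patients at ≤5 years) × (share of those with DR). The documents give neither share. With 5% to 30% for the first and 0% to 20% for the second, the result runs from 0 to 1000 × 0.30 × 0.20 = 60 patients. Against an assumed 300 patients in another DR class, power for a 0.5 SD difference is 20% with 5 patients, 34% with 10, 58% with 20 and 94% with 60.

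**The case against.** **The regression may already do this.** Duration is among the recorded clinical data, so it is a natural covariate in the planned model, and a condensed article may leave its form to a fuller document. This stands in part. A reader might infer that the study nowhere analyses duration as a continuous variable, but the documents do not show that. The loss is established only for the class comparisons. Those are, however, the comparisons listed under Main outcome measures.

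**The size of the loss depends on assumptions.** It does. The protocol sets no effect size, and at a correlation of 0.20 the loss is about 2 points. Linearity favours the 1-degree-of-freedom test; under a threshold or plateau the classes may lose less. The spline covers those shapes, and so answers the question of shape better than three means.

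**The classes are legitimate strata.** They are prespecified, do not overlap, cover all durations and are easy to read. This stands, and it is a reason to keep them for description.

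**A tempting stronger reading.** A reader might infer that hardly any patients will have DR within 5 years of diagnosis, and that the duration comparison in DR eyes is therefore close to uninformative. The documents do not support this. They give no DR frequency and no distribution of duration, and the assumed ranges lead anywhere from 0 to 60 patients. Even with a very small first class, the contrast between the other two DR classes would remain.

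**Conclusion.** The point holds as an improvement to the analysis; nothing in the plan is contradictory here. Two of the four main comparisons coarsen a variable that is available in continuous form. Under a roughly linear relation and uniform durations the classes keep 65% to 83% of the variance in duration, and less under the two skewed distributions tried (62% and 51%).

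The cost in power is substantial for weak relations (22 points at ρ = 0.12 and 14 at ρ = 0.15, with n = 600 and 74% kept) and negligible from ρ = 0.20. All of these inputs are assumptions. The loss of shape, and of any trend beyond 15 years, does not depend on them.

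The exploratory aim and the absence of a power target limit the weight of the power argument. They do not weaken the argument about shape, because describing a relation is what an exploratory study is for. A small DR class at ≤5 years is a possibility to check against observed counts and not an established defect.

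**What to change.** In Statistical methods and Main outcome measures, name continuous duration as the main duration analysis. For each main outcome, fit one model with duration (a linear term plus a restricted cubic spline), DR status and a duration by DR term, adjusted for age. This replaces the two class-based tests and addresses both duration questions together.

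Keep the three classes for descriptive tables, and report the number of patients and eyes in each of the six DR by duration cells. Merge classes in those tables only if the observed counts require it.

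The cost is a few lines of wording and a modest amount of analysis. Date of diagnosis and duration are already recorded, so no new data, visits or patients are needed.

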### Interventions

#### Systemic data

Systemic status of the diabetic disease will be evaluated in routine clinical care examinations in the Diabetes Unit of the Endocrinology service, and clinical data collected will include: Demographics, date of diagnosis, duration of disease, treatment type, glycaemia, HbA1c levels, concomitant pathology (hypertension, etc.), body mass index, lipid profile (total cholesterol, triglycerides, HDL-cholesterol, LDL-cholesterol) and kidney function tests (urinary albumin excretion, estimated filtration glomerular rate).

#### Ocular data

Patients identified in the Endocrinology service will be referred to the Ophthalmology service. In the eye clinics, a complete eye examination will be performed. Clinical data collected in this visit will include: Best-corrected visual acuity, biomicroscopy, intraocular pressure, retinal fundus exam and biometry (IOL Master, Carl Zeiss Meditec, Dublin, CA). A comprehensive battery of OCT and OCTA images will be performed, described below.

### OCTA images scanning protocols

Two optical coherence tomography angiography devices will be employed to obtain OCTA retinal images. Further retinal imaging techniques including fundus retinography (Optomap, Optos, Inc) and structural OCT will be performed.

#### Cirrus HD-OCT (Carl Zeiss Meditec, Dublin, CA, USA)

A 6 × 6 mm OCT macular cube centered in the fovea will be captured, and measurements of retinal and choroidal thicknesses in each subfield of the Early Treatment Diabetic Retinopathy Study (ETDRS) grid will be obtained using the device’s manufacturer built-in software. Using the Angioplex OCTA, images will be captured with the 3 × 3, 6 × 6 and 8 × 8 mm scanning protocol (Fig. 2). This image will be subsequently loaded in the image processing software.

**Fig. 2 Fig2:**
[figure not shown]
Examples of OCTA image datasets collected for each individual patient and eye included in the study (3 × 3, 6 × 6 and 8 × 8 mm scan sizes, Angioplex, Cirrus HD-OCT, Carl Zeiss Meditec, Dublin, CA, USA). Similar images were obtained with a different swept source device for each study eye (3 × 3, 6 × 6 and 9 × 9 mm, Triton Deep Range Imaging -DRI- OCT, Topcon Corp, Topcon, Japan)

#### Triton deep range imaging (DRI) OCT (Topcon Corp, Topcon, Japan)

A 12 × 9 mm OCT macular cube centered in the fovea will be captured, and measurements of retinal and choroidal thicknesses in each subfield of the Early Treatment Diabetic Retinopathy Study (ETDRS) grid will be obtained using the device’s manufacturer built-in software. Using the OCTA scanning protocol, a 6 × 6 mm image of the scanned cube centered in the fovea will be obtained. This image will be subsequently loaded in the image processing software.

Controls: For validity of readings of the study device and as an internal normative database, a cohort of 100 normal eyes (controls) from a pool of healthy volunteers with clear media and without retinal disease will undergo retinal imaging and OCTA-derived measurements will be calculated. The mean intensity of the foveal avascular zone (FAZ) of these eyes will be determined to establish the reference for detection of flow in the macula.

### Data collection and data management

Systemic and ocular data will be obtained from the hospital electronic medical records system and will be collected in a pseudoanonymized database by the study team for confidentiality reasons. The OCT and OCTA images will be stored in the hospital servers and a back-up copy will be exported to encrypted hard disk drives that will remain physically in the hospital. All access to this data will be restricted only to the study team, and a formal data monitoring committee will not be constitued. Data sharing agreements will be specifically obtained from the sponsor of the study (Fundació Clínic para la Recerca Biomedica, at Hospital Clínic of Barcelona) by the study team for image analysis collaborations with third parties, as specifically indicated in the written informed consent signed by study participants.

### Main outcome measures

Main outcome measures to be determined will be A) parafoveal and perifoveal vessel density, B) total avascular area, and C) foveal avascular zone.

Comparisons will be made between these measurements in:
controls and type I DM eyes,type I DM eyes with no DR and DRtype I DM eyes with no DR and different duration of disease timeframestype I DM eyes with DR and different duration of disease timeframes

Secondary outcome measures include subgroup analysis of vessel density by treatment type, glycemic control (glycaemia and HbA1c), metabolic index, body mass index, and kidney function tests.

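### The duration objective covers all type 1 DM patients, but every listed duration comparison is made within a DR stratum and is likely to understate the overall gradient

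*Protocol article*

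**What the plan says.** All references are to the protocol article.

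- **Background, objectives.** Three descriptive objectives are listed: patients against controls, patients with against without DR, and "and patients with type 1 DM at different times of disease progression". The third carries no condition on DR status.
- **Study groups.** The duration classes are A (5 years or less), B (more than 5 and less than 15) and C (15 or more). They are nested in DR status: "Both groups will be classified by duration of diabetic disease".
- **Main outcome measures.** Four comparisons are listed: controls against DM, no DR against DR, "DM eyes with no DR and different duration of disease" timeframes, and "DM eyes with DR and different duration of disease" timeframes.
- **Background, rationale.** Prolonged glucose exposure is described as "damaging the retinal vessels and affecting the retinal blood flow in a time-dependant manner".
- **Statistical methods.** A multivariate regression will relate OCTA measurements to clinical characteristics. The section names neither duration nor DR status as a term. Duration is among the data collected (Systemic data), and the abstract's Methods names it as a factor to be related to the OCTA parameters.

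**The concern.** The third objective asks how the capillary network differs with time since diagnosis in type 1 DM as a whole. The listed comparisons ask how it differs with time among eyes that have not developed DR, and separately among eyes that have. These are different questions.

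They can also have different answers. The rationale has exposure time damaging vessels, and the Discussion expects OCTA changes to precede the step from no DR to mild DR. On that account duration leads to damage, damage leads to DR, and OCTA measures the damage. Long-duration eyes still free of DR will tend to be less damaged than long-duration eyes in general, and short-duration eyes that already have DR will tend to be more damaged than short-duration eyes in general. Both tendencies shrink the difference between class C and class A inside a stratum.

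At stake is the reading of the result. A weak gradient in both strata could be reported as little change with duration when selection on DR status accounts for part of it, and no listed comparison would show the unselected gradient beside it. The Discussion links the findings to possible use of OCTA in screening.

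**Working it through.** **1. Objective against comparison.**

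| Objective (Background) | Matching entry (Main outcome measures) |
|---|---|
| DM and controls | controls against DM eyes |
| with and without DR | no DR against DR |
| different times of progression | duration within no-DR eyes; duration within DR eyes; none in all DM eyes |

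The third row has no unrestricted match. This needs no assumption.

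**2. The plan's only related figure.** The Sample size section gives 2000 × (1 − 0.50) = 1000 patients, which reproduces. It is a recruitment estimate. The article states no effect size, SD or DR prevalence, so every input below is an assumption.

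**3. Three-class model (3,000,000 simulated eyes).** Duration class g = 0, 1, 2 (A, B, C) in equal numbers.
- Damage: L = 0.3g + e, with e of SD 1.
- DR liability: wL + dg + √(1 − w²) × noise. DR is the top 30%.
- Vessel density: V = −L − h × DR + 0.5 × noise.
- Contrast: mean V in C minus mean V in A.

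Here w is how far damage drives DR, d is a path from duration to DR that bypasses damage, and h is DR's own effect on density. With h = 0 the all-eyes contrast is −2 × 0.3 = −0.60. With w = 0, d = 0.6, h = 0.5, DR prevalence is 0.12 in A and 0.50 in C, giving −0.60 − 0.5 × (0.50 − 0.12) = −0.79, in line with the simulated −0.794.

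| w | d | h | All eyes | No DR (share) | DR (share) |
|---|---|---|---|---|---|
| 0 | 0.6 | 0 | −0.600 | −0.602 (100%) | −0.604 (101%) |
| 0.5 | 0 | 0 | −0.600 | −0.525 (87%) | −0.489 (81%) |
| 0.5 | 0.6 | 0 | −0.600 | −0.246 (41%) | −0.047 (8%) |
| 0.8 | 0.3 | 0 | −0.600 | −0.179 (30%) | 0.039 (−7%) |
| 0 | 0.6 | 0.5 | −0.794 | −0.600 (76%) | −0.598 (75%) |
| 0.5 | 0.6 | 0.5 | −0.829 | −0.242 (29%) | −0.049 (6%) |

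Repeating the last row with DR prevalence at 15% gives 49% and −1%; at 50% it gives 15% and 14%.

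**4. Continuous-duration model (2,000,000 draws).** Duration is uniform over 0 to 40 years, DR is present in 30%, the correlation of duration with damage is 0.3 to 0.5, and that of OCTA with damage is 0.4 to 0.6. The table gives the duration slope as a share of the all-eyes slope.

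| Correlation of DR liability with damage | No DR | DR |
|---|---|---|
| 0.7 to 0.9 | 61–80% | 42–70% |
| 0.4 | 92–94% | 89–91% |

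How closely DR tracks damage governs the size.

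**5. Regression with DR as a covariate.** In the model of step 4 with correlation 0.7 to 0.9, the DR-adjusted duration slope was 55–77% of the unadjusted slope. Adjusting for DR brings the same attenuation as stratifying on it.

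**The case against.** The case on the other side has real force.

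- **The regression may already do this.** Duration is collected and named in the study's aim, and nothing confines the model to one stratum. A reader might infer that duration is analysed only inside DR strata; the article does not support that for the plan as a whole. What remains is that the regression is not linked to the third objective, and that it answers that objective only if DR status stays out of the model. The full covariate list may fairly be left to an analysis plan. The mismatch in step 1, however, lies in the article's own list of comparisons.
- **The no-DR comparison is a proper question.** The aim is a "non-invasive screening tool for detecting early changes in the perifoveal vascular network", and change before visible DR can be studied only in eyes without DR. This stands: the comparison is not an error and need not be demoted.
- **Understatement is not certain.** This also stands. If DR is unrelated to damage given duration and has no effect of its own, the attenuation vanishes (first row of step 3). That scenario sits poorly with the article's premises, but the documents cannot exclude it.
- **Selection is partial.** A reader might picture the long-duration no-DR group as a resistant remnant. In the model of step 4 with correlation 0.7 to 0.9, 60–65% of eyes at 15 years or more are still free of DR, and 9–19% of those at 5 years or less have it. That is a shift in who is compared. It does not by itself imply a flat gradient.

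**Conclusion.** The point holds in a limited form. As a matter of text, the third objective is unrestricted by DR status and no listed main comparison answers it without conditioning on DR. As a matter of inference, the stratified contrasts are likely to be smaller than the overall one, because the article itself describes the retinal blood flow effect as time-dependent ("affecting the retinal blood flow in a time-dependant manner") and expects OCTA change to come before DR.

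The size is open. In the scenarios of step 3, all of which assume that duration does cause damage, the share of the all-eyes contrast retained was 15% to 100% in no-DR eyes and about −7% to 101% in DR eyes. These are illustrations on assumed inputs; neither a single percentage nor a claim that the bias is certain can be drawn from the documents. The study is cross-sectional and exploratory, so this is an inexpensive improvement in how it answers its own objective, and not a flaw in the data to be collected.

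**What to change.** 1. In Main outcome measures, add a comparison of duration classes A, B and C in all type 1 DM eyes, neither stratified by nor adjusted for DR status, and name it as the answer to the third objective. Equivalently, state in Statistical methods that the regression will estimate duration as a continuous variable in all type 1 DM eyes with DR status left out of that model.
2. Keep both DR-stratified comparisons as they are.
3. Add one sentence saying that those two are conditional on DR status, so that a weak or flat gradient there is not by itself evidence of no change with duration.

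The cost is a few lines of text and one further analysis of data already being collected. The planned 1000 patients, the visits and the imaging do not change.
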